### 9.3.2 Visit 1 - Intervention

Treatment will be continued for all subjects according to the international AHA/ASA guidelines^44^ and according to local standard practice.

After eligibility has been confirmed, the responsible investigator will access a 24-hour password protected, internet-based enrolment system to enrol the subject into the clinical investigation. The patient will be transported immediately to the angiography suite for subsequent treatment or further diagnostics. In the angiography suite non-contrast cranial syngo DynaCT Sine Spin imaging must be performed within four hours after the MDCT scan and before any other intervention or operation.

# 10. SAFETY

According to Swiss legislation there is no general obligation for the systematic documentation of adverse events (AEs) in medical device category A clinical investigations.^51^

**Adverse Events (AEs)** deemed to be related to the procedure under investigation (Adverse Device Effect) and all **Device deficiencies (DD)** are collected, fully investigated and documented in the source documents and appropriate case report forms (CRF) during the entire investigation period, i.e., from patient’s enrolment until the last CIP specific procedure, including a safety follow-up period of 24 hours. Serious adverse events which lead to death of the patient within 24 hours of enrolment will also be collected, fully investigated, and documented in the source documents and appropriate case report forms (CRF) independently of their causality.

## 10.1 Definition and Assessment of (Serious) Adverse Events and other safety related events

*See Appendix C- US Protocol Amendments

**Adverse Event (AE)** (Art. 2 Abs 57 MDR)

Any untoward medical occurrence, unintended disease or injury or any untoward clinical signs (including an abnormal laboratory finding) in subjects, users or other persons whether or not related to the MD.

**Serious Adverse Event (SAE)** (Art. 2 Abs 58 MDR)

Any adverse event that led to any of the following:

(a) death,

(b) serious deterioration in the health of the subject that resulted in any of the following:

(i) life-threatening illness or injury,

(ii) permanent impairment of a body structure or a body function,

(iii) hospitalisation or prolongation of patient hospitalisation,

(iv) medical or surgical intervention to prevent life-threatening illness or injury or permanent impairment to a body structure or a body function,

(v) chronic disease,

(c) foetal distress, foetal death or a congenital physical or mental impairment or birth defect.

Note: planned hospitalization for pre-existing condition, or a procedure required by the CIP, without a serious deterioration of the health status of the subject, is not considered an SAE. (ISO14155)

**Device deficiency** (Art. 2 Abs 59 MDR)

Inadequacy of a medical device related to its identity, quality, durability, reliability, safety or performance, of an investigational device, including malfunction, user errors and inadequate information supplied by the manufacturer.

**Malfunction** (ISO14155)

Failure of an investigational device to perform in accordance with its intended purpose when used in accordance with the instructions for use or the CIP.

**Device deficiency with Serious Adverse Device Effect (SADE) potential** (Art. 80 Abs 1 letter c MDR; ISO14155)

Any device deficiency that might have led to a serious adverse event if appropriate action had not been taken, intervention had not occurred, or circumstances had been less fortunate.

**Adverse Device Effect (ADE)** (ISO14155)

Adverse event possibly, probably or causally related to the use of an investigational device or procedures.

**Serious Adverse Device Effect (SADE)** (ISO14155)

Adverse device effect (ADE) that has resulted in any of the consequences characteristic of a serious adverse event.

**Unanticipated Serious Adverse Device Effect (USADE)** (ISO14155)

Serious adverse device effect (SADE) which by its nature, incidence, severity or outcome has not been identified in the current version of the risk analysis report.

**Causal Relationship of SAE** (MDCG 2020-10/1)

A causal relationship towards the medical device or the procedure of the investigation should be rated by the PI and the Sponsor as follows:

- **Not related:** The relationship to the device or procedures can be excluded.
- **Possible:** The relationship with the use of the investigational device is weak but cannot be ruled out completely. Alternative causes are also possible.
- **Probable:** The relationship with the use of the investigational device seems relevant and/or the event cannot reasonably be explained by another cause.
- **Causal relationship:** The serious event is associated with the investigational device or with procedures beyond reasonable doubt.

## 10.2 Adverse events categorization

The adverse events are categorized by the PI and the Sponsor using the following algorithm:

Does the AE meet the seriousness criteria?

- - No, it is not serious
    - - Is the relationship to the device or the procedure possible, probable or causal?
      - No: non-related AE
      - Yes: ADE
  - Yes, it is serious: SAE
    - - Is the relationship to the device or the procedure possible, probable or causal?
      - No: non-related SAE
      - Yes: SADE
  - Is it anticipated (within expected type, severity and frequency of the complications)?
    - - No: unanticipated SADE (USADE)
      - Yes: anticipated SADE (ASADE)

## 10.3 Documentation and reporting in Medical Device Category A clinical investigations

According to Swiss legislation there is no general obligation for the systematic documentation of adverse events (AEs) in medical device category A clinical investigations.^51^

*See Appendix C- US Protocol Amendments

**Adverse Events (AEs)** deemed to be related to the procedure under investigation (at least possible) and **Device deficiencies (DD)** are collected, fully investigated and documented in the source documents and appropriate case report form (CRF) during the entire investigation period, i.e. from patient’s enrolment until the last CIP specific procedure, including a safety follow-up period of 24 hours. Serious adverse events which lead to death of the patient within 24 hours of enrolment will also be collected, fully investigated, and documented in the source documents and appropriate case report forms (CRF) independently of their causality. These events will be coded according to the MedDRA system.

Documentation of SAEs by the PI includes diagnosis or symptoms, start and stop dates of event, event treatment, event resolution, assessment of seriousness and causal relationship to MD and/or investigation procedure (Art. 32 ClinO-MD, ISO14155).

Documentation of DDs by the PI includes description of event, start date, investigational device information, action taken with regard to the investigational device, and whether the DD led to an AE. The Sponsor shall review all DDs and determine and document in writing whether they could have led to a SAE (DD with SADE potential) (Art 32. ClinO-MD, ISO14155).

The Sponsor provides the CA and the CEC with the documentation at their request (Art. 32 ClinO-MD).

The information on AEs, DDs and SAEs will be collected through the eCRF. The follow-up period will be 24 hours after the intervention. Since the intervention has no invasive character (besides minor radiation), we do not expect the occurrence of any SAEs related to the medical device (or procedure/intervention) under investigation. For the occurrence of deterministic radiation damage (i.e. direct radiation damage) an radiation above 200 mSV must be applied. There is no scenario in which this could occur due to internal safety measures within the medical device under investigation. The internal safety measures are a) CAREwatch: Dose area product and the reference air kerma are shown on the screen, b) CAREmonitor: Display of the cumulated skin entrance dose of the currently radiated patient skin area and c) CAREguard: acoustic dose alert when the accumulated reference air kerma exceeds configurable thresholds.

### 10.3.1 Foreseeable adverse events and anticipated adverse device effects

There are no foreseeable adverse events or anticipated adverse device effects in this investigation.

### 10.3.2 Reporting of Safety related events Reporting to the Sponsor

All SAEs, device deficiencies and health hazards that require measures are reported to the Sponsor by the PI (or authorized designee) within 24 hours after becoming aware of the event. Device deficiencies are assessed regarding their potential to lead to an SAE.

Reporting to the Competent Ethics Committee:

The following events are to be reported to the CEC promptly (Art. 33 ClinO-MD):

1. any serious adverse event which has a causal relation with the MD (rating at least possible), comparator or procedure/test method or where a causal relation appears to be possible (SADE);
2. any device deficiency which, in the absence of appropriate measures or intervention or in less favourable circumstances, could have led to serious adverse events (DD with SADE potential);
3. any new information relating to an event already notified under points (1) and (2).

In order to ensure prompt notification, the Sponsor may initially submit an incomplete notification. If safety and health hazards that require measures must be taken immediately during the conduct of the investigation, the Sponsor notifies the CEC within 2 days of these measures and the circumstances which made them necessary (Art. 34 ClinO-MD).

**Periodic safety reporting (Art. 35 ClinO-MD):**

An Annual Safety Report (ASR) is submitted by the Sponsor to the CEC, yearly (Art. 35, 38 ClinO-MD). The ASR contains a list of all SADEs and DDs and a report on their degree of seriousness, causal relationship with the MD and procedure and on subjects’ safety. This includes all SADEs and DDs which have happened abroad.

### 10.3.3 Follow-up of (Serious) Adverse Events

SAEs if at least possibly related to the medical device under investigation, SADEs and SAIs will be followed until resolution or stabilization. Ongoing events must be documented at 14 days intervals until resolution. Subjects with ongoing events at trial termination will be further followed up until recovery or until stabilization after termination for another 14 days.

# 11. STATISTICAL METHODS

Detailed methodology for summaries and statistical analyses of the data collected in this study will be documented in a statistical analysis plan (SAP).

The SAP will be finalized before database closure and will be under version control at the Clinical Trial Unit, Department for Clinical Research, University Hospital Basel.

## 11.1 Hypothesis

Null hypothesis: Sensitivity and specificity of non-contrast contrast syngo DynaCT Sine Spin to detect the presence (sensitivity) and absence (specificity) of intracranial hemorrhages are inferior to MDCT. Inferiority is given when one of the lower bounds of the 95%-CI of sensitivity and specificity are equal or lower than 95%.

Alternative hypothesis: Sensitivity and specificity of non-contrast contrast syngo DynaCT Sine Spin to detect the presence (sensitivity) and absence (specificity) of intracranial hemorrhages are non-inferior to MDCT. Non-inferiority is given when both lower bounds of the 95%-CI of sensitivity and specificity are higher than 95%.

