However, the widespread implementation of this direct to angiography workflow has been impended by the difficulty of differentiating between ischemic and hemorrhagic stroke with FDCT.^39, 40^ As it is not possible to differentiate between ischemic and hemorrhagic stroke without brain imaging, it is of pivotal importance that hemorrhage exclusion can be performed safely and reliably with native FDCT imaging as well. A missed intracranial hemorrhage, i.e. an hemorrhagic stroke (which make up between 15 and 20% of all severely affected stroke patients according to an analysis of the Swiss Stroke Registry) could have potentially dramatical (and lethal) consequences due to different treatment strategies.^41^ Up till now this was only evaluated in retrospective studies, which showed very high sensitivity and specificity in the detection of intracranial hemorrhage with the last generation of FDCT.^6, 18^ However, prospective high-quality studies with large patient cohorts on this topic are still missing. We further did not find any ongoing studies on clinicaltrials.gov or within the WHO trial registry.

Therefore, we aim with this study to investigate if non-contrast syngo DynaCT Sine Spin imaging is non-inferior to non-contrast MDCT imaging regarding its sensitivity and specificity for the detection of intracranial hemorrhages. Non-contrast syngo DynaCT Sine Spin imaging will be deemed non-inferior if the lower bound of the 95%-confidence interval (95%-CI) of the sensitivity is above 95% and the lower bound of the 95%-CI of the specificity is above 95% (pre-defined non-inferiority margin). If non-inferiority could be established, this would guarantee for a safe triage of stroke patients. We are confident, that if our study shows non-inferiority of non-contrast syngo DynaCT Sine Spin imaging it will pave the way for the widespread implementation of the above described direct to angiography workflow, allowing more AIS patients to live a self-sustained, independent life after their stroke. Due to the high burden of disease any measurement of improvement is of high need. Conversely if our study fails to establish non-inferiority of non-contrast syngo DynaCT Sine Spin imaging for the detection of intracranial hemorrhage, it might prevent patients from undergoing harmful treatments.

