## 11.2 Determination of Sample Size

To calculate the sample size, hypothetical experiments were simulated. We estimate a sensitivity of 99% and a specificity of 98% of non-contrast syngo DynaCT Sine Spin imaging for the detection of intracranial hemorrhage as it was described for the predecessor generation in the literature.^48^ To account for variation, diagnostic performance of hypothetical readers was varied with rates of 98.5%, 99% and 99.5% for sensitivity and 97.5%, 98% and 98.5% for specificity. Rates were attributed randomly with equal chance.

Sensitivities and specificities of readers were generated from correlated binary random variables. To reproduce the correlated readings between readers, a high correlation between binary random variables was chosen. This assumption was made based on the literature and judgement of the principal investigators. We further simulated lower correlations which showed consistently that an approach using a high correlation is more conservative (i.e., leading to a higher sample size). Generated outcomes were vectors with 1 (true positive) and 0 (false negative) for sensitivity and 1 (true negative) and 0 (false positive) for specificity. The quotient of the occurrences of 1 and the number of cases with/or without a bleeding being sensitivity and specificity, respectively. In case sensitivity or specificity was 100%, a false negative (for sensitivity) and a false positive (for specificity) was introduced into the generated output. This enabled to still fit a model (see below).

To represent “difficult cases”, i.e. patients who present with an isolated infratentorial intracranial hemorrhage, we introduced a subpopulation of patients for whom the performance of raters was only 70% sensitivity. We chose n = 14 patients based on an additional sample size calculation. With this subsample, there is an 80% chance (power) that the lower bound of the 95%-CI of a sensitivity of 70% is higher than 50%. However, we assume that the subsample substantially overrepresents the incidence of difficult cases in the study population (see section 6.1). Therefore, we attributed a lower weight in the model to each difficult case.

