It was tested whether the lower end of the 95%-CI did not fall below the prespecified margins. For sensitivity and for specificity this was 95%. The 95%-CI of sensitivity and specificity were calculated by fitting a generalized linear random-effects model with a logit link function. Random-effects variables were patient and reader, outcome variable was the randomly generated binary vector. To converge to model estimates, the algorithm of the “nloptwrap”-optimizer was applied.

From the model, the lower end of the 95%-CI of the fixed-effect intercept was extracted and transformed to percent. The 95%-CI was calculated by the method of Wald. If the lower ends of the 95%-CIs of sensitivity and specificity both did not fall below a pre-defined margin, the experiment was rated as “successful”. The percentage of “successful” experiment out of all experiments characterizes the study power. Each sample size, n_i=1,..,19_ = 80,…,260 was evaluated by sampling 999 times n_i_ individual samples with a range of readers from 1 to 7.

If the total weight of “difficult cases” is set at 0.02, the number of difficult cases at n= 14, the power at 90% the number of readers at 6, and the drop-out rate at 5%, a total of **252 patients** (238 patients without drop-outs) must be recruited. The patients must be pre-selected in a ratio of hemorrhage positive to hemorrhage negative of 1:1, i.e., 126 patients are presenting with and 126 patients without intracranial hemorrhage (out of which 14 present with an isolated infratentorial intracranial bleeding). The number of readers was set based on our model calculations since with a lower number of readers the sample size fluctuated substantially (over 100%). The needed sample size however stabilized at a range of 5 to 7 readers. With this number of readers, the sample size fluctuated only by 10% (with 7 readers being the lowest and with 5 the highest).

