### 11.5.2 Primary Analysis

The primary analysis will be based on the FAS. As described for the sample size calculation, a generalized linear random-effects model with a logit link function will be fit. The explanatory variables ’reader’ and ’patients’ will be random effects. Difficult cases will be weighted with 2%. From the fixed-effect intercept of sensitivity and specificity, the 95%-CIs will be calculated applying the method of Wald. Sensitivity will be calculated based on the results of all core-lab readers of the non-contrast syngo DynaCT Sine Spin scans of all patients for which the ground truth was deemed to be hemorrhage positive. Specificity will be calculated based on the results of all core-lab readers of the non-contrast syngo DynaCT Sine Spin scans of all patients for which the ground truth was deemed to be hemorrhage negative. It will be tested whether both the lower bound of the 95%-CI of the sensitivity and specificity are higher than the margin of 95%.

All results will be reported in concordance with the STARD guidelines.^20^

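### Section 11.1 equates failure to show non-inferiority with inferiority and leaves no inconclusive outcome

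*Protocol*

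**What the plan says.** Section 11.1 attaches a decision sentence to each hypothesis. Under the null: "Inferiority is given when one of the lower bounds of the 95%-CI of sensitivity and specificity are equal or lower than 95" per cent. Under the alternative: "Non-inferiority is given when both lower bounds of the 95%-CI of sensitivity and specificity are higher than 95" per cent. Neither sentence refers to the true sensitivity or specificity as the quantity being tested, and no third outcome is named.

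Other sections use the same criterion but define success only. The primary objective (synopsis and section 4.2) says when FDCT will be deemed non-inferior and nothing about the opposite case. Section 11.5.2 says: "It will be tested whether both the lower bound of the 95%-CI of the sensitivity and specificity are higher than the margin of 95" per cent. It draws no conclusion if the test is not met.

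The background in section 3.1 also discusses an unsuccessful trial, in the phrase "Conversely if our study fails to establish non-inferiority", and adds that this might spare patients harmful treatment.

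**The concern.** Both lower limits above 95%, or at least one at or below 95%: these two cases cover every possible result. Section 11.1 names the first non-inferiority and the second inferiority, so an interval that includes 95% but extends well above it goes to inferiority by definition. That is the usual error of taking the absence of proof as proof of the opposite.

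The cause is that the null is written on a sample quantity. A hypothesis should concern the true sensitivity and specificity, and the confidence limit is the tool for testing it. When the limit itself defines the null, failing to reject becomes the same thing as the null being true.

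At stake is how a failed trial would be read. The device is a candidate triage test. Calling it inferior when the data were merely too imprecise would be a wrong conclusion, and section 11.1 as written leads there.

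**Working it through.** **Inputs from the protocol**
- Margin (11.2): "For sensitivity and for specificity this was 95" per cent.
- Interval (11.2): "The 95%-CI was calculated by the method of Wald". I take it as two-sided, so one-sided 2.5% per endpoint, with both endpoints required to pass.
- Assumed accuracy (11.2): "We estimate a sensitivity of 99% and a specificity of 98% of non-contrast syngo DynaCT Sine Spin imaging".
- Design (11.2): "the power at 90% the number of readers at 6, and the drop-out rate at 5" per cent.
- Sample size (11.2): 238 patients before drop-out, 252 after, in a 1:1 ratio.

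**Reproducing the plan's figure.** 238 / 2 = 119 per side; 119 / 0.95 = 125.3, rounded up to 126; 2 × 126 = 252, as stated. The 238 and the 90% power come from a simulation whose reader correlation is described only as high, so they cannot be recomputed exactly.

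**Size from the stated power.** Section 11.2 defines power as the share of simulated trials in which both lower limits clear the margin. The remaining share is what 11.1 calls inferior: 1 − 0.90 = 0.10. About 10% of trials of a device at 99%/98%, both above the margin, would get that label. No outside assumption is needed.

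**A single result.** 119 patients × 6 readers = 714 readings, treated as independent for illustration only. With 25 errors:
- estimate 689 / 714 = 96.5%
- logit = ln(689/25) = 3.316; standard error = √(1/689 + 1/25) = 0.2036
- limits on the logit scale 3.316 ± 1.96 × 0.2036 = 2.917 and 3.715, or 94.9% and 97.6%

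The estimate exceeds the margin and most of the interval lies above it, yet 11.1 says inferiority.

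**A device somewhat below plan but above the margin.** I simulated 119 patients × 6 readers per endpoint with a cluster-robust logit-Wald lower limit. Reader correlation was varied as an assumption, and the weighting of difficult cases was left out. The two endpoints use different patients, so pass probabilities multiply.

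| Assumed correlation | Pass at 99% | Pass at 98% | Joint power at 99%/98% | Pass at 97% | Labelled inferior at 97%/97% |
|---|---|---|---|---|---|
| 0 | 1.000 | 0.994 | 99.4% | 0.744 | 1 − 0.744² = 45% |
| 0.1 | 0.996 | 0.898 | 89.4% | 0.539 | 1 − 0.539² = 71% |
| 0.2 | 0.976 | 0.794 | 77.5% | 0.420 | 1 − 0.420² = 82% |
| 0.5 | 0.797 | 0.505 | 40.2% | 0.239 | 1 − 0.239² = 94% |

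In this simplified model the row at 0.1 comes closest to the stated 90% power.

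**The case against.** The sentence stands inside the null hypothesis and mirrors the one under the alternative, so it can be read as a clumsy statement of when the null is retained. The passages that govern the conclusion (synopsis, 4.2, 11.5.2) define success only, and the SAP, not shown here, may treat interpretation properly. The 10% is simply the planned type II error, which rewording leaves as it is.

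Much of this stands. Three stronger readings are not supported:
- A reader might infer that the protocol orders a failed trial to be reported as proof of inferiority. No section contains such a reporting rule.
- A reader might take section 3.1 as resting on the same error. It speaks correctly of failing to establish non-inferiority, and its consequence is hedged. Not adopting a triage test that was not shown to clear the margin needs no claim of inferiority.
- A reader might size the problem with an exact limit on one reading per patient (119 per side, at most one error passes), which gives 98% labelled inferior at 97%/97% and 90% at 98%/98%. The same rule gives joint power of only 0.666 × 0.310 = 21% at 99%/98%, against the stated 90%. It does not describe this trial.

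What the objection cannot remove is the wording. Section 11.1 is where the hypotheses are fixed, its two sentences leave no room for an inconclusive result, and an SAP that follows it would inherit the fault.

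**Conclusion.** Section 11.1 is wrong as written. It defines the null on observed limits and equates failure to show non-inferiority with inferiority. The firm measure of size is 10%: the share of trials at the assumed 99%/98% that would be labelled inferior, directly from the stated power. At a true 97%/97% the share is 45% to 94% for assumed reader correlations from 0 to 0.5, and 71% at the value that roughly matches 90% power. These simulated figures rest on a simplified model and on a correlation that the protocol does not give.

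The fault lies in the hypothesis wording and in how a failed trial would be read. The rule for declaring success is sound and is not in question.

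**What to change.** Restate section 11.1 on the true parameters:
- H0: true sensitivity ≤ 95% or true specificity ≤ 95%.
- H1: true sensitivity > 95% and true specificity > 95%.

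Keep the success rule, and replace the sentence on inferiority with: *If either lower bound is ≤ 95%, non-inferiority has not been shown; this alone does not establish inferiority.*

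A separate inferiority claim based on an upper limit below 95% is optional, and the trial does not need it. If one is added, either endpoint could trigger it. With both true values exactly at 95%, the chance of a false claim would be about 1 − 0.975² = 4.9%, assuming independent endpoints and nominal coverage.

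Section 3.1 needs no change. The cost is a few lines of text in one section, with nothing to recalculate: the 95% margin, the 252 patients, the type I error and the 90% power stay as they are.
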